#### Initial home visit with support coach

During the first in home session, the support coach reviews the tailored feedback form with the FCCP. Then, using the ME protocol, the support coach identifies the FCCP’s readiness to make a change, helps the FCCP set a goal related to one topic, identifies potential barriers to completing the goal, and discusses plans to overcome those barriers. The FCCP also documents her level of motivation and confidence to make this change (on a scale of 0–10). Throughout each of these steps, the support coach creates a collaborative environment that is supportive of the FCCP’s own autonomy and self-efficacy. The support coach listens to the FCCP’s responses and reflects back the change language that she hears the FCCP say.

The support coach documents the results of the session on a data form including the topic the FCCP chose to work on, the specific goal for the topic, any stated barriers to achieving the goal, the FCCP’s level of motivation and confidence for achieving the goal, and any, “change talk,” the support coach heard during the conversation about the FCCP’s readiness and reasons to make the change. The coach also records the date and time of the phone call for the following month. This process is repeated each month for 7 additional months during the monthly phone calls with the FCCP and support coach See Support Coaching by Phone.

At the end of the visit, the Intervention group FCCPs receive a set of active play toys to use with the children, including “pool” noodles, hula hoops and foam hoop holders, a tunnel, bean bags, soft balls, feather-light balls, and plastic colored spots. The toys are also accompanied by a set of videos and activity cards that demonstrate activities utilizing the toys.

#### Tailored newsletters

For each of the 8 months of the intervention period, participants receive a tailored newsletter covering a different theme based on the topic areas they selected during the initial home visit and/or the phone coaching sessions and the content of those conversations. The first newsletter packet, mailed 1–2 weeks after the in-person visit, begins with a cover letter that is individually tailored with the name of the FCCP, the name of their support coach, the FCCP’s topic choice (chosen during the support coach home visit) and the FCCP’s current practices related to this topic (based on data taken from the surveys and/or observation). This tailored letter also reminds the FCCP of the time for their upcoming scheduled support coach call, and includes a brief description of the FCCP’s expressed barrier, goal for the month, and comments gathered from the last conversation with their support coach. The rest of the newsletter packet includes 4–5 pages of content about the FCCP’s chosen topic (See main topics in Table 1). If the FCCP mentioned a barrier related to this topic during the conversation with the coach, they also receive a barrier page providing suggestions on how they might overcome the barrier. Barriers covered in newsletters include those most commonly mentioned in our formative research including time, cost, taste, anticipated mess, resources needed and others. (See an example newsletter in Additional file 2: Figure S3).

#### Videos

Along with the mailed newsletter, FCCPs also receive a short, 3–5-min video related to their chosen topic with audiovisual content in the language of their choice (English or Spanish). The videos show actual FCCPs demonstrating best practices with the children in their care with simple, straight-forward tips and explanations for making changes. Segments include: testimonials from other FCCPs, cooking demonstrations of healthy recipes, scenarios displaying problem-solving, and demonstrations of activities to do with children. FCCPs choose to receive the videos in one of three ways: 1) A mailed DVD; 2) An emailed link to view the video online; 3) A text message containing a link to view on their smartphone.

#### Support coaching by phone

After receiving their first tailored newsletter, FCCPs receive monthly phone calls (approx. 20–25 min) with their support coach for the next 7 months. At the start of each phone call, support coaches ask if the FCCP received their newsletter and video, and if they read or watched the material. Then, the support coach again uses the ME approach to discuss thoughts and concerns and to check in on the FCCP’s progress in completing their goal and assist in addressing barriers. The FCCP also selects a new topic for the next month, establishes a goal and discusses possible barriers. The support coaches again listen for “change talk” from the FCCP including reasons they want to make a change. The support coaches document the conversation on a data form, including notes about the completion of goals for the previous month, responses about the usefulness of the previous newsletter and video (from a scale of very useful to not at all useful), the selected new topic, and associated goal, barriers, change talk and motivation and confidence (on a scale of 0–10). This data form is then incorporated into the computerized expert system to generate the next tailored mailing (cover letter, newsletter and video) to be sent to the FCCP. All phone calls between the FCCP and the support coach are recorded for quality assurance purposes.

#### Group meetings

Support group meetings are held approximately every 6 weeks at a local community location such as a library or church. FCCPs in the Intervention group are invited to attend the meetings led by the Intervention group coaches. The meetings, which last approximately 90 min, include a light meal and demonstration of an activity related to nutrition and/or physical activity education that FCCPs can do with the children in their care. The meetings also serve as a time for social support where FCCPs discuss challenges and solutions they face while working on different monthly topics. Support coaches are present and lead the activities, but mainly serve as facilitators.

#### Intervention components for the comparison group

FCCPs randomized into the Comparison group receive the same intervention components, dose and intensity as those in the Intervention group, except the content is related to reading readiness and early literacy skills. As with the Intervention group, the Comparison group components include the tailored feedback form, the in-person home visit and seven monthly calls from the support coach using ME, 8 tailored newsletters and videos mailed monthly, and the group meetings (approximately every 6 weeks), with content related to reading readiness and early literacy skills rather than nutrition and physical activity. The FCCP selects which of eight intervention topics related to reading readiness they want to work on each month and when they hope to begin. As with the intervention group, they get a packet starting with a tailored cover sheet, however, they do not receive individually tailored content within the newsletter packet nor barrier pages. The intervention content was adapted from the Reading Rockets and Coloring Colorado curriculum materials [95–97]. Materials were reviewed and revised as needed by experts in early childhood education at the University of Connecticut. Topics for the newsletters and videos include why reading is important, getting ready to read, reading aloud, wordless picture books, building vocabulary, early writing skills, interactive play, and creating a home library. Instead of a set of activity toys, FCCPs in the Comparison group receive a set of 10 books including 3 wordless pictures books. FCCPs can choose to receive books in English and/or Spanish.

### Evaluation and analysis

The Healthy Start evaluation includes process evaluation measures to assess intervention delivery and satisfaction as well as effect evaluation of outcome and behaviors to assess changes in primary, secondary and exploratory outcomes.

#### Process evaluation and analysis

Process evaluation measures assess participant satisfaction and fidelity of intervention delivery, including staff adherence to intervention protocols and dose of the intervention received by participants.

##### Participant satisfaction

Participant satisfaction is assessed on the 8- and 12-month follow-up surveys. Questions assess the perceived helpfulness of all intervention components including the support coach, videos, newsletters, group meetings, toys and toy video and activity cards (or books for the Comparison group). Questions also include how much the providers feel that the newsletters were created just for them and were easy to read and understand. FCCPs are also asked how well the support coach helped them to make changes in their FCCH and respected efforts to improve their FCCH. Providers in both groups are asked what they liked most, what they liked least, and how the Healthy Start program can be improved. They are also asked to list changes they have made in their FCCH and changes to their own nutrition, physical activity, or screen time habits because of the Healthy Start program. In addition to the survey questions FCCPs who attended the group meetings fill out a brief evaluation form at the end of the session, which queries helpfulness and usefulness of the sessions, what they liked about the group meeting, possible improvements to be made, and convenience of the location and time.

##### Fidelity

Adherence to the intervention protocol is measured in several ways. Project staff track mailings of the newsletters and videos as well as implementation of group meetings. Attempts to connect with FCCP as scheduled are recorded by support coaches; these logs are used to assess coaches’ effort to connect with FCCPs. Support coaches also complete forms to document what was discussed on each call. Support coaches record all phone calls; at least 10% of the recordings with FCCPs are reviewed to assess ME skills and fidelity with subject content.

Dose is measured as the number of newsletters and videos read and watched, group meetings attended, and toys/books used as reported by FCCP on the 8- and 12-month surveys. Additionally, the software used to send video links to FCCP via email or text tracks if the link was clicked; the website that hosts the videos online also tracks how many times a video is watched by the FCCP. Support coach call tracking records enumerate attempts to reach FCCP and call completions, as well as the length of each completed call. Support coaches or staff members facilitating group meetings record FCCP attendance. Additionally, providers are asked about any additional training they received outside the study related to nutrition or physical activity to evaluate potential contamination between comparison and Intervention groups.

Process evaluation data will be quantified as counts and proportions for each intervention component. Relationships between intervention dose and outcome measure changes will be studied using linear regression models.

#### Effect evaluation and analysis

##### Sample size considerations

The proposed final sample size of 60 FCCHs per experimental group with 3 children per site was chosen to detect differences in primary outcomes consistent with changes found in our Healthy Homes, Healthy Families pilot study, as well as effect sizes in [name] and other published research in child care centers [47, 49, 93, 98]. We anticipate that our proposed final sample of 60 FCCHs per condition with power of 0.8 or greater and alpha of .05 will allow for detection of effect sizes of at least 0.25 serving of fruits and vegetables per day and 3 oz of 100% fruit juice or sugary beverage, as well as increase of 2.1% time in moderate/vigorous physical activity or 2.2% screen-time. To account for expected attrition of 10%, we will recruit 66 homes in each experimental group (total *n* = 132).

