#### Provider eligibility criteria

To be eligible for the study, participants must be a FCCP within 60 miles of Providence, RI, have been operating a FCCH for at least 6 months with plans to remain in operation for at least 1 year; read and speak Spanish or English; have a working phone; have at least one 2–5-year-old child in their care for at least 10 h per week, and who eats at least one meal and one snack prepared by the FCCP during their time at the FCCH. In addition, FCCPs cannot plan to close their FCCH for more than 3 consecutive weeks during the year following their enrollment in the study.

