### Outcome evaluation protocols and measures

#### Evaluation overview and randomization procedures

Evaluation measures are conducted with each FCCP at baseline, with the same measures administered when the 8-month intervention is completed and again after 4 months (approximately 12 months after the intervention begins). At baseline, eligible FCCPs complete the first part of the baseline survey on the telephone. Upon completion of this survey, time is scheduled for the project field coordinator to conduct an in-person visit at the FCCH. During this visit, the field coordinator completes the enrollment process, which includes review of the study protocols and expectations, completion of the informed consent and implementation of the second part of the baseline survey. The field coordinator also leaves written consent forms for the parents of the age-eligible children in the FCCH. For a child to participate in the evaluation, parents must give consent for their child to have diet observed by project staff, wear an activity monitor and/or undergo anthropometric measurement. When at least one signed parent consent form is obtained giving permission for at least one of the measures, the two-day observation is scheduled with the FCCH.

The two-day observation by research staff members includes measurement of the physical and social environment of the FCCH as well as children’s dietary intake. During these visits, staff members also conduct anthropometric measures of the eligible children whose parents consented. Consented children also wear accelerometers during the 2 days to measure their activity. Evaluation staff are blinded to group assignment to reduce measurement bias. All measures are described in detail below.

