Once FCCPs complete the entire baseline survey and in-home observation, they are randomized into either the Intervention or Comparison group. FCCPs are randomized in pairs matched based on their primary language spoken and the number of eligible children within the age range of 2–5 years in their FCCH. The data manager randomly assigns all participants to experimental groups using a Microsoft Excel randomization function after which participating providers are notified of their assignment by a phone call from the project coordinator. Evaluation staff members are not made aware of the intervention group assignment during any aspect of data collection preparation or conduct in the field. Participation in the Healthy Start study, and all data collected through observation or other means are stored in a secure, password protected network or in locked file cabinets.

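### 66 homes per arm less 10% is 59.4, not 60, and the entry rules do not secure the 3 children per home on which the power statement rests

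*Protocol article*

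**What the plan says.** In the protocol article, the section on sample size considerations sets the target: "The proposed final sample size of 60 FCCHs per experimental group with 3 children per site". It claims that this sample, "with power of 0.8 or greater and alpha of .05 will allow for detection of effect sizes" listed for fruit and vegetables, juice or sugary drinks, moderate/vigorous activity and screen time. It then adds: "To account for expected attrition of 10%, we will recruit 66 homes in each experimental group", 132 in total.

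Three rules elsewhere in the article determine how many children a home contributes:

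- Provider eligibility criteria: the provider must "have at least one 2–5-year-old child in their care for at least 10 h per week".
- Evaluation overview and randomization procedures: consent is by measure, in that "parents must give consent for their child to have diet observed by project staff, wear an activity monitor and/or undergo anthropometric measurement". The observation is booked as follows: "When at least one signed parent consent form is obtained giving permission for at least one of the measures".
- Same section: randomization follows the baseline survey and observation, and "FCCPs are randomized in pairs matched based on their primary language spoken and the number of eligible children". No minimum number of measured children is stated.

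The section on the two-day observation also provides for homes with more than 3 consented children, by sending additional observers.

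**The concern.** Two features of the sample-size paragraph do not sit well with the rest of the article.

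First, the recruitment figure does not follow from its own inputs. Adding 10% to the final number is not the same as allowing for a loss of 10% of those recruited.

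Second, the power statement uses a flat 3 children per home, while the entry rules set a floor of one child with consent for one measure. A home whose only consent is for anthropometry, which feeds the exploratory outcomes, could be randomized and counted among the 132 without contributing to diet quality or accelerometer activity, the primary outcomes. Those outcomes are defined as changes, so a child analysed on within-child change needs the measure at baseline and again at 8 or 12 months. The only loss allowance stated is the 10%, and it is used to inflate the number of homes.

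At stake is the claim of power of 0.8 or greater. If the mean number of contributing children falls below 3, the effective sample is smaller than the one behind that claim.

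**Working it through.** **Attrition.** Inputs from the sample-size paragraph: 60 final homes per arm, 10% attrition, 66 recruited.

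- The plan's figure: 60 × 1.10 = 66, so 132 in total. This reproduces it.
- Homes left after 10% loss: 66 × 0.90 = 59.4 per arm (118.8 in total, against 120).
- Homes needed to keep 60: 60 / 0.90 = 66.7, so 67 per arm (134 in total).
- Loss that 66 does cover: 1 − 60/66 = 9.1%.

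**Children per home.** The article gives no standard deviation, no intraclass correlation (ICC) and no expected mean of measured children, so the power statement cannot be reproduced. What can be shown is how power moves with the mean number of children.

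Assumptions: two-sided alpha 0.05; k homes per arm, each with m contributing children (equal cluster sizes); ICC 0.05 to 0.5; and 60 × 3 giving exactly 80% power.

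- Effective children per arm: E = k·m / (1 + (m − 1)·ICC).
- Standardized effect with 80% power at 60 × 3: d = (1.96 + 0.842)·√(2/E₀), where E₀ is E at k = 60, m = 3.
- Power in any other case: Φ(d·√(E/2) − 1.96).

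Worked case at ICC 0.2:

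- E₀ = 180/1.4 = 128.6, so d = 2.802 × √(2/128.6) = 0.349.
- With m = 2, E = 120/1.2 = 100.0.
- Power = Φ(0.349 × √50 − 1.96) = Φ(0.51) = 69.5%.

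| Homes per arm × children | ICC 0.05 | ICC 0.1 | ICC 0.2 | ICC 0.3 | ICC 0.5 |
|---|---|---|---|---|---|
| 60 × 3 (anchor) | 80.0% | 80.0% | 80.0% | 80.0% | 80.0% |
| 59.4 × 3 | 79.6% | 79.6% | 79.6% | 79.6% | 79.6% |
| 60 × 4 | 88.6% | 87.5% | 85.7% | 84.3% | 82.5% |
| 60 × 2.5 | 73.5% | 74.3% | 75.6% | 76.6% | 78.1% |
| 60 × 2 | 64.9% | 66.6% | 69.5% | 71.8% | 75.2% |
| 60 × 1.5 | 53.7% | 56.3% | 60.8% | 64.7% | 70.7% |

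The attrition slip costs 0.4 points at any ICC. The number of contributing children matters far more, in either direction. At a mean of 2, matching the effective sample of 60 × 3 would take 86 final homes per arm at ICC 0.05, falling to 68 at ICC 0.5.

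**The case against.** The strongest reply is that one child is an eligibility floor, not an expected mean. The observation procedures plan for homes with more than 3 consented children, no cap is stated, and matching on the number of eligible children shows that variation was anticipated. A mean of 3 is compatible with every rule in the article, and a mean above 3 would raise power. This stands. A reader might infer that 60 × 3 is not what the plan will deliver, or that 3 is close to the maximum. The article supports neither reading.

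The 80% anchor is also an assumption. The article says 0.8 or greater, so there may be slack, and without a standard deviation or ICC a reader cannot conclude that power is definitely below 80%. That stands too.

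Next, 3 per site is described as part of a final sample, so it might already be net of child-level loss. The wording allows this, but the article does not say so. The only loss it quantifies is the 10%, and that is used to go from 60 homes to 66.

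Finally, a condensed article may leave consent rates and per-measure calculations to the full protocol. Their absence is therefore not the point. The point is that the article fixes a figure of 3 which its own entry rules do not protect.

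On the attrition arithmetic, the fair reply is that 0.6 of a home per arm is within ordinary rounding. Its effect is indeed negligible, but the stated figures still do not follow from each other.

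**Conclusion.** The concern holds in two parts of unequal weight.

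The attrition figure is wrong as written: 66 homes less 10% leaves 59.4 per arm, not 60. This is certain and minor.

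The assumption of 3 children per home is not secured by the entry rules, and the stated loss allowance covers homes only. This is a risk to power and not a demonstrated shortfall. Its size depends on a mean that the article does not give: about 74–78% power at 2.5 children, 65–75% at 2, and 83–89% at 4. These ranges rest on an assumed ICC of 0.05 to 0.5, equal cluster sizes and exactly 80% power at 60 × 3.

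**What to change.** - Correct the attrition statement: either give the final sample as 59 homes per arm for 66 recruited, or recruit 67 per arm to retain 60.
- Restate the detectable differences separately for the diet and accelerometer outcomes, using the expected number of children per home who contribute that measure at both baseline and follow-up. Showing 1.5, 2, 2.5, 3 and 4 would cover both directions.
- State the ICC used, and show the expected child-level loss (partial consent, absence on observation days, children leaving care) beside the 10% home-level loss.

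The cost is one recalculated paragraph. No extra enrolment is needed if the final sample is restated as 59; choosing 67 adds one matched pair. The downside is that the stated figure may become slightly less favourable.

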#### Exploration of group assignment

Demographic and other baseline characteristics will be compared between groups to confirm that the random assignment resulted in statistically similar groups. Any variables found to be different between groups at baseline will be included in final models. Child-level outcomes will be adjusted for clustering at the FCCH level using generalized estimating equation (GEE) models with exchangeable correlation matrices.

##### Primary outcomes

Our primary outcomes are changes in children’s dietary quality and changes in children’s physical activity. Dietary quality is measured using the 2015 Healthy Eating Index (HEI) score, which is calculated based on data collected during the two-day observation using the DOCC. DOCC data collected in the field are reviewed for completeness and entered into the NDSR. The NDSR data are then inputted into Statistical Analysis Software (SAS) (SAS Institute, Cary, NC) to calculate HEI component scores and total HEI-scores. The HEI components scores include total fruit, whole fruit, total vegetable, dark green and orange vegetables and legumes, total grain, whole grain, milk, meat and beans (adequacy) and saturated fat, sodium, added sugars, and solid fats (moderation). These components are derived using established scoring methods written as publicly available USDA SAS codes [68]. SAS codes add food group equivalents and divide over 1000 cal, creating a normalized variable per adequacy or moderation component. Adequacy components are positively scored, where a higher intake results in an increased score, while moderation components are reversed scored, where a lower intake results in an increased score. Total HEI scores are generated by combining adequacy and moderation scores for a maximum score of 100.

Children’s physical activity is measured using accelerometer data. After being removed from the children in the FCCH, accelerometers are brought back from the field and entered into the computer to be scored in batches with the Actilife software (Actigraph [99]), using appropriate cut points and energy expenditure formulas for 2–5 year old children. [100, 101]. Time filters are applied based on the times that field staff record affixing and removing the accelerometers each day, as well as the times the children begin and end their naps with or without wearing the device. Scored data files describe the amount of time each child spends in sedentary, light, moderate, and vigorous activity across the 2-day observation period, not including naptime.

